## Abstract

**Background:**

Although the benefits of supervised physical activity programs in cardiac rehabilitation have been well documented, the amount of physical activity often drops quickly after the end of the supervised period. This trial (registered as ISRCTN77313697) will evaluate the effectiveness of an experimental intervention based on habit formation theory applied to physical activity maintenance.

**Methods/Design:**

Cardiovascular patients (*N* = 56) will be individually randomized into two groups. Two supervised physical activity (SPA) sessions per week will be offered to the first group for 20 weeks. Progressively autonomous physical activity (PAPA) will be offered to the second group as follows: 10 weeks of the same supervised program as the SPA group followed by 10 more weeks in which one supervised session will be replaced by a strategy to build and sustain the habit of autonomous practice of physical activity. The primary outcome is the amount of physical activity measured by the International Physical Activity Questionnaire (IPAQ; Craig et al., Med Sci Sport Exercises 35(8):1381–95, 2003). To compensate for the limited capacity to recruit subjects, multiple IPAQ measurements will be made (at T0, T5, T7, T9 and T12 months after the start of the intervention) and analyzed using the mixed model approach. We will also assess changes in physical and physiological indicators, automaticity of the physical activity behavior, motivation and quality of life. Last, we will assess the cost-effectiveness for each type of program.

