### Sample size

The sample size was calculated using the simulation method of PASS 14 software (NCSS, Kaysville, USA) for power analysis with a mixed model. An alpha risk of 5 % and a bilateral hypothesis were taken into account for the power analysis. We estimated the expected scores of the participants in each arm of our study on the basis of the results of large-scale studies [34, 35, 38] that assessed PA behavior maintenance after CR with a questionnaire providing an average score of PA minutes per week. Given the linear effect of time, the change in PA behaviors after SPA suggested that the weekly time spent in PA behavior would be reduced by 5 min very month following the intervention. This result was used to infer the PA level of the group at each measurement point post-program. Several studies have shown that interventions designed to promote maintenance can lead to stabilized or even slightly increased PA behaviors over time (e.g., [2, 29, 34, 38]). We therefore predicted no change in the amount of PA behavior for the PAPA group after the intervention. The power analysis used a similar average score immediately after the intervention of 200 min/week for both groups, a general between-subject variability of 90 min/week, and an autocorrelation of the repeated measures of .55. ([name], [name], [name]. (unpublished manuscript). Testing the effect of text messaging cues to promote physical activity habits: A worksite-based exploratory intervention). The results after 1000 simulations indicated that 50 evaluable participants (25 participants in each arm) would be required to find the time-by-condition interaction effect with an 80 % power level. Assuming about 10 % of patients mistakenly included, lost to follow-up or withdrawing from the study, we randomized 56 participants (28 participants in each of the two arms).

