#### Behavioral measures

PA behavior will be assessed using a self-report questionnaire extensively used in the literature, the International Physical Activity Questionnaire (IPAQ) [14] at time (T) 0, T5, T7, T9 and T12 months. The questionnaire responses will be computed as energy requirements defined as METs (multiples of the resting metabolic rate). Based on previous research in other chronic diseases (e.g., [31, 32]), a subsample using a GT3X+ accelerometer will comprise 30 % of the participants selected randomly from among volunteers. According to this meta-analysis, an acceptable level of agreement between IPAQ and GT3X+ indicated a small to moderate association (r = .29). They will wear the GT3X for one week (score in METs) at T0, T5 and T12 in order to check whether the self-reported PA measure correlates with the objective PA measure in the context of our study. The PA adherence will be assessed by reporting on the participation in the two supervised sessions per week and the autonomous session.

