#### Statistics and data analysis

All statistical analyses will be performed with a 5 % alpha risk or 95 % confidence interval using SAS 9.3 (SAS Institute, Cary, NC, USA) or SPSS (IBM Statistics, Armonk, NY, USA). No interim analysis will be performed. The normality of quantitative data will be evaluated using a graphical method (frequency histogram and quantile-quantile plot) and a Shapiro-Wilk test [21]. To test the primary hypothesis on PA behavior maintenance, a mixed model procedure will be conducted to take into account the non-independence of the repeated IPAQ measures grouped within participants and the non-independence of the participants grouped in different centers. It should be noted that this type of analysis is highly recommended for repeated measures analysis [39, 48]. The repeated measures will be considered as a longitudinal fixed factor (measurements at T5, T7, T9 and T12). The condition (PAPA vs. SPA) representing the criterion of the analysis will be considered as a fixed effect in the model. The interaction between these two factors will be examined to test whether the change in PA behaviors after the end of the intervention differs depending on the arm of the trial. To control for individual differences in PA levels, the initial level of PA (IPAQ at T0) will be included as a fixed covariate. The intercept will be defined as a random factor that can vary for each participant and for each study center.

For the secondary objectives, we will first check for incomplete or missing data. Missing data at random will be imputed using the multiple imputations method. Sensitivity analyses will be used to address the impact of imputation on conclusions. A general linear model (GLM) will test the hypotheses, including the time of measurement (within-subject factor), the experimental condition (between-subject factor) and the interaction between these two factors.

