## Discussion

Cardiovascular patients are generally willing to take part in CR, but unfortunately they do not systematically have the opportunity to do so (80 % of our sample). The PAPA intervention is designed to complement secondary prevention programs or replace them for those who cannot easily participate. The intervention aim is to provide cardiovascular patients with an opportunity to progressively learn, adopt and maintain PA behaviors.

The data from this study will be used to assess the impact of the *As du Coeur* intervention just after the end of the intervention (T5). We do not expect significant differences between the PAPA group and the fully supervised group at this point. Indeed, the fully supervised group will have more supervised sessions that the autonomous group (two per week versus one per week in the second half of the intervention). Based on the linear trend in the PA measures made in the months following the end of the intervention, we expect to find a decline in PA (negative linear slope of the time effect) post-intervention only for the SPA group. We expect that patients of the PAPA group will either maintain the same level (null slope) or even increase their PA (positive slope) in the months following the end of the intervention. Despite our low sample size due to a limited recruitment capacity, it is important to recall that this hypothesis can still be adequately tested with reasonable power using a mixed model approach, as simulation studies of the power in mixed model have shown that it typically increases with repeated measurements [23]. However, we will carry out exploratory analyses to test whether the PAPA intervention also leads to greater automaticity and motivation for PA, higher quality of life and better physical condition compared with the SPA intervention. Another limitation of the study can be the used of the sport motivation scale to assess participant’s motivation in the context of PA as motivation for sport and physical activity can differ.

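### Repeated IPAQ readings are presented as compensation for limited recruitment, but for the stated slope contrast T7 and T9 add only about 9% information (about two patients per arm), and 0 to 2.3% under AR(1)

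*Protocol article*

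**What the plan says.** All references are to the protocol article.

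- **Abstract, Methods/Design:** "To compensate for the limited capacity to recruit subjects, multiple IPAQ measurements will be made". The readings are to be analysed with a mixed model.
- **Discussion:** the low sample size is acknowledged, but the hypothesis is said to be testable with reasonable power because "simulation studies of the power in mixed model have shown that it typically increases with repeated measurements".
- **Behavioral measures:** the IPAQ is given "at time (T) 0, T5, T7, T9 and T12 months". The physical-condition tests and the psychological measures are taken at T0, T5 and T12, so T7 and T9 are visits added for the IPAQ.
- **Statistics and data analysis:** "The repeated measures will be considered as a longitudinal fixed factor (measurements at T5, T7, T9 and T12"). Baseline enters only as an adjustment: "the initial level of PA (IPAQ at T0) will be included as a fixed covariate". The random part is an intercept per participant and per centre.
- **Sample size:** "An alpha risk of 5 % and a bilateral hypothesis were taken into account for the power analysis". In the supervised arm, "the weekly time spent in PA behavior would be reduced by 5 min very month following the intervention"; no change is predicted in the PAPA arm. Both arms start from 200 min/week after the intervention, with SD 90 and "an autocorrelation of the repeated measures of .55". The result is 25 evaluable patients per arm for 80% power on the time-by-condition interaction.

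**The concern.** Extra readings raise power a good deal when they all estimate the same constant difference between arms. This trial does not expect one. The Primary research objective predicts no difference at the end of the intervention and a gap that opens afterwards, so the target is a difference in slopes. For a slope, the value of a reading depends on how far in time it lies from the average visit. T7 and T9 fall 2 and 4 months into a 7-month span whose mean is 3.25 months, so they carry little. T0 is a covariate and does not inform change after T5.

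If the gain is small, the article tells readers that the main weakness of a small trial has been offset when most of it remains. A null result could then be read as evidence against the PAPA programme rather than as a consequence of low precision.

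**Working it through.** **Inputs.** Times since the end of the intervention are 0, 2, 4 and 7 months (Statistics and data analysis). SD 90, correlation .55, slopes −5 and 0 min/week per month, 25 per arm and two-sided 5% are from Sample size. The article gives neither the structure nor the time unit of .55. Exchangeable correlation (which a random intercept implies) and AR(1) are therefore both tried as assumptions.

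**The plan's own figure.** With exchangeable .55, a patient's slope has variance σ²(1 − ρ)/Sxx, where Sxx is the sum of squared deviations of the visit times.
- Four visits: deviations −3.25, −1.25, 0.75 and 3.75; Sxx = 10.5625 + 1.5625 + 0.5625 + 14.0625 = 26.75.
- Variance = 8100 × 0.45 / 26.75 = 136.3. Standard error of the slope difference = √(2 × 136.3 / 25) = 3.30. Ratio = 5 / 3.30 = 1.51.
- Power (noncentral t, 48 df) = 31.7%. The stated 80% does not reproduce. AR(1) readings give 16% to 30%. The inflation 50 / 0.9 = 55.6, rounded to 56, does reproduce.

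The power shortfall is a separate matter. The information gain below is a ratio and does not depend on the SD, the effect size or the number of patients.

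**What T7 and T9 add, exchangeable .55.**
- T5 and T12 only: Sxx = 2 × 3.5² = 24.5; variance 3645 / 24.5 = 148.8; standard error 3.45; power 29.5%.
- Gain = 26.75 / 24.5 − 1 = 9.2%. Equivalent patients = 25 × 0.092 = 2.3 per arm. Power moves from 29.5% to 31.7%.

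**The same under AR(1), by generalised least squares.**

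| .55 applies per | Gain from T7 and T9 |
|---|---|
| month | 2.3% |
| visit | 1.7% |
| 2 months | 0.4% |
| mean visit gap (2.33 months) | 0.2% |
| 7 months | 0.0% |

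**Sensitivity (exchangeable .55).**
- Dropout after T9 of 10%, 20% or 30%: gain 10.7%, 12.9% or 16.0%.
- Arms separate early and then plateau (T5 against the mean of three later readings): variance factor 2 falls to 1 + 1/3, a gain of 50%.
- Slopes that vary between patients (SD 5 to 10 min/week per month): gain 7.8% to 5.3%.
- Time as a categorical factor with a 3-df interaction test: power falls from 29.5% with T5 and T12 only to 21.1% with all four visits.

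**A wider comparator: one follow-up reading.** In common units, the four-visit slope carries 26.75 / 0.45 = 59.4 and an unadjusted T12 comparison carries 7² = 49, so the plan gains 21%. A T12 comparison adjusted for T0 carries 49 / (1 − 0.55²) = 70.3, with power about 36%. This takes .55 for the T0–T12 correlation and, as the article does, equal means at T5.

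**The case against.** The strongest reply is that the abstract credits all the IPAQ measurements and does not name T7 and T9. T5 plus T12 is already repeated measurement, so the fairer comparator is a single reading. Against an unadjusted T12 comparison the plan gains 21%, or about five patients per arm (25 × 0.21). That stands, and a reader who inferred that there is no compensation at all would go too far. It does not rescue the claim: a single T12 comparison adjusted for T0 does at least as well as the planned slope test (about 36% against 31.7%) without the visits in between.

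The Discussion's general statement is also true as far as it goes. Power does rise with T7 and T9, and for a constant level difference three follow-ups instead of one, adjusted for T5, give about 1.75 times the information. But the article uses that statement to support a contrast for which the rise is about two percentage points.

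The 9% rests on linearity and complete data. The Background says activity drops quickly once rehabilitation ends, and under an early plateau T7 and T9 would be worth much more. That also stands. The article's own planning assumption, however, is a linear decline of 5 min/week per month, and its Discussion expects a linear trend.

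A reader might also take the IPAQ–accelerometer correlation of .29 in Behavioral measures as proof of large week-to-week noise at the ends of the slope. It does not show that: agreement between two instruments can be low through systematic bias or because they measure different things. The article gives no recall window for the IPAQ either, so no argument from one is made here.

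**Conclusion.** The concern holds in a limited form. For the contrast the article states, T7 and T9 add about 9% information under exchangeable .55 (about two patients per arm, power about 30% to 32%) and 0 to 2.3% under AR(1). Late dropout raises the exchangeable figure to 11% to 16%, and an early plateau raises it further. These figures rest on the Sample size inputs and on an assumed correlation structure.

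The article therefore claims a property that its design has only to a small degree. It would be wrong to conclude that the visits are useless: they show the shape of the decline and keep partial data from patients who leave before T12.

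**What to change.** 1. In the abstract and the Discussion, remove the wording on compensation and reasonable power. Alternatively, state the gain for the slope contrast, for example: *under an exchangeable correlation of .55, the T7 and T9 readings add about 9% information on the difference in linear slopes, equivalent to about two patients per arm; under a first-order autoregressive correlation they add 0 to 2.3%.* Keep T7 and T9, and give their purpose as the shape of the decline and partial data from dropouts. This costs a few sentences.

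2. Optional, if still feasible: repeat the IPAQ about a week apart at T12, and at T5 if that visit is not past (the article reports screening in October 2014 and randomization in the past tense). Average the two readings, or add a visit-within-patient random effect. With a participant intercept alone, the model would treat two readings a week apart as independent.
   - The gain depends on the unknown share of within-person variance that is short-term noise. Assume that share runs from 0 to 100%, that the rest has a correlation decaying over 1 month, and that the repeat falls a week inside the T5–T12 span. Slope information then rises by about 4% to 80% with repeats at both ends and by 3% to 37% at T12 only.
   - Even the best case gives power of about 51%, so this does not restore the stated 80%.
   - The cost is one or two more questionnaires per patient and probably a protocol amendment.

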**Discussion:**

If proven to be effective, the PAPA intervention, which requires fewer supervised sessions, should provide a cost-effective solution to the problem of physical activity maintenance in cardiac rehabilitation.

## Background

Cardiovascular disease (CVD) is the leading cause of death worldwide, accounting for 30 % (16.7 million) of all deaths [45]. Coronary heart disease makes up the highest proportion of CVD mortalities and is projected to show an increase of 16.6 % by 2030 [24]. Strategies to reduce the impact of CVD have thus become crucial. Cardiac rehabilitation (CR) is a complex secondary prevention intervention to reduce of risk of cardiovascular disease and to promote the adoption and maintenance of healthful behaviors in CVD patients. Exercise has consistently been identified as an integral component of CR in the secondary prevention guidelines [3].

Supervised physical activity (PA) programs for CVD patients effectively improve the level of physical activity [42] but PA maintenance once supervision has ended is often disappointing, typically showing a linear decline over time. A comprehensive search of the literature on post-CR PA indicates that this behavior quickly drops when CR ends (e.g., [18]). In 2003, Yu et al. evaluated the long-term changes in exercise capacity in cardiac patients who participated in an 8-week center-based CR program. At the 2-year follow-up, the improved exercise capacity had declined to the point where it was similar to that of the inactive control group. A meta-analysis by Chase [12] reviewed 14 intervention programs to maintain or increase PA after CR. Although maintenance was enhanced using behavioral or cognitive methods, none of the programs focused on habit formation. Yet recent work has identified habit as the main predictor of maintaining health behaviors [20, 36]. While enacting a behavior that is regulated by motivation typically requires deliberate effort, habits are thought to be triggered automatically and may thus occur in the absence of awareness, conscious control, mental effort and deliberation [46]. This would explain why habits are particularly well-suited to guiding behavior in everyday life, as high cognitive demand (e.g., time pressure, distractions, stress, fatigue) reduces the capacity to act on deliberative processes.

Nevertheless, habit formation is a long process that requires many repetitions of the same behavior in the same context [26]. It is assumed that successful habit formation depends on the frequency and consistency of the contextual cues associated with the desired behavioral response [46]. A few studies have started to develop interventions based on the habit framework. In a recent trial [25], volunteers wanting to lose weight were randomized to one of two conditions: one in which a leaflet listing 10 simple diet and activity behaviors was provided, as well as encouragement for context-dependent repetition, and a control condition of a no-treatment waiting list. After 8 weeks, the intervention group had lost 2 kg compared with 0.4 kg in the control group. Interestingly, the effect did not vanish over time but became stronger, with a 3.8-kg loss for the intervention group at the end of the 32-week follow-up period. Moreover, actions that had been initially difficult to carry out became easier to maintain. Another randomized controlled trial recently replicated this effect on weight loss in a primary care setting with a larger sample over a 24-month follow-up period [5]. In the PA domain, a recent study (Phillips & Gardner, [33]) confirmed an earlier one (Verplanken & Melkevik [43]) demonstrating that an important factor of habitual exercise concerns the decision to go. Phillips and Gardner [33] confirmed this finding and called the decision exercise instigation. They further demonstrated that the habit strength of exercise instigation was the only predictor of exercise frequency.

Habit theory assumes that habits are context-dependent, and this might explain why behaviors learned in CR centers are hard to sustain outside the centers in the real living environment. These patients are often insufficiently physically active during leisure time prior to diagnosis (e.g., [16]). Moreover, upon diagnosis, they face psychological barriers to exercise related to fears of death, perceived exercise risks or lack of self-efficacy (e.g., [22]). While direct supervision in CR centers has the advantage of providing a safe environment with trained coaches and the possibility for social exchange, it does not reproduce the patients’ living context. At the end of center-based CR, patients return to their everyday environments, which more often than not are characterized by sedentary habits. Reviews comparing the level of PA in center-based versus home-based interventions have indeed shown that center-based interventions ultimately end with PA levels similar to those of home-based interventions once the program is over—and with lower PA levels at long-term [15, 40]. For example, the study by Ramadi et al. [35] showed that the exercise level increased similarly in the center-based and home-based groups during the program period. However, from post-CR to the 1-year follow-up, exercise capacity remained unchanged in the home-based CR participants, whereas the center-based CR group demonstrated a decline in exercise capacity. Based on this finding, a program that favors the transition between the cardiac rehabilitation center and home appears to be needed.

### Study Objectives

#### Primary research objective

We hypothesize that a progressively autonomous PA (PAPA) intervention for people with cardiovascular disease that promotes habit formation in an everyday-life context will result in better PA maintenance than a fully supervised PA (SPA) intervention. We do not expect any difference between groups immediately after the end of the intervention, but we assume that the difference will emerge over time, with the PAPA group showing a slower and smaller decline in PA behaviors after the end of the PA intervention than the SPA group.

#### Secondary research objectives

Exploratory analyses will assess the differences between the two groups in motivation for PA, automaticity of PA behavior and quality of life. We will also compare the evolution in the patients’ physical condition. Last, we will evaluate the cost-effectiveness of the two interventions. We hypothesize that the PAPA program promoting habit formation will result in better physical condition, motivation, automaticity of PA behavior and quality of life at the end of follow-up compared with the SPA program. We also hypothesize that the PAPA program will cost less than the SPA program.

